#### Ascertainment of outcomes

##### Baseline data collection

The baseline questionnaire will include questions on socio-demographic and economic characteristics, bath time safety practices, bath time supervision and satisfaction with hot water supply. Families completing the baseline questionnaire will be offered an incentive (free bath mat or first aid kit) as incentives have been shown to increase response rates [22]. The design of the baseline questionnaire will be informed by individual face to face interviews with a sample of approximately 15 families residing in rented social housing. A purposive sample of families will be obtained to include families with differing maternal educational levels, different family composition, including children of differing ages, families with differing ethnic origins and differing levels of disadvantage. Interviews will take place in the families' homes and will explore issues surrounding bath safety and bath time supervision.

The first 50% of participants recruited to each arm will have their bath hot tap water temperature measured at recruitment to the trial. Water temperatures will be determined by direct measurement by a qualified plumber from City Building (Glasgow) Limited Liability Partnership, using a Type K thermocouple thermometer and rounded immersion probe. The temperature of the hot water supply will also be measured at an outlet other than a bath and without a TMV e.g. wash basin. This will enable detection of other methods to reduce hot water temperature such as reducing water heater thermostat settings.

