#### Follow-up data collection

##### Primary outcome measure

A random sample of 15 families in each arm, who did not have their tap water temperature measured at baseline, will be chosen to have their tap water temperature measured at 3 months post fitting of TMVs and a separate random sample of 15 families in each arm will be selected to have their tap water temperature measured at 12 months post fitting of TMVs. Families will be offered a £10 voucher for use in local stores to increase response rates for water temperature measurements [22]. Measurements will be made in the same way as at baseline.

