### Sample size

Ten families per arm are required to detect a reduction in the mean bath hot tap water temperature from 60.4 degrees Celsius (SD 9.1)[11] in the control group to 46 degrees Celsius in the intervention group, with 90% power and a 5% significance level (2 sided). Allowing 33% for losses to follow-up, 15 families in each arm will be randomly selected for tap water temperature testing at 3 and 12 months post valve installation (intervention arm) or randomisation (control arm). A different 15 families in each arm will be tested at 3 and 12 months.

For the secondary outcome measures, 50 families in each arm would provide:

• 80% power at the 5% significance level (1 sided) to test the hypothesis that the proportion of TMVs removed, disabled or whose temperature setting was adjusted did not exceed 6.5% if the true proportion of valves removed, disabled or adjusted was 1%.

• 80% power at the 5% significance level (2 sided) to detect a difference in the proportion of families agreeing that their bath hot tap water temperature was sufficiently hot from 90% in the control arm to 67% in the intervention arm.

To allow for losses to follow-up, a total of 120 participants will be recruited.

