### Randomisation

After giving informed consent, families will be randomised to treatment arms. The randomisation schedule will be generated by the trial statistician using a computerised random-number generator in Stata [23], using a permuted block design with a random block size. Equal numbers will be allocated to the two groups. No stratification will be used. Group allocations will be placed in sequentially numbered, opaque, sealed envelopes. These will be opened sequentially by a researcher independent of the research team after participants have consented. The independent researcher will inform the study research fellow of the allocation who will inform GHA of the allocation. The research fellow will write to each family informing them of the allocation and provide details of how they will be contacted by GHA to organise water temperature measurement and TMV fitting.

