### Analysis

The analysis will conform to a pre-specified analysis plan. Bath hot tap water temperatures will be described using the mean and standard deviation, or median and interquartile range, depending on the distribution of temperatures. The primary analysis will compare temperatures between treatment arms using an unpaired t-test to estimate the difference between the means and its 95% CI, assuming assumptions for undertaking these analyses are met. If assumptions are not met and no suitable transformation can be found, temperatures will be compared between treatment arms using the Mann-Whitney U test.

An intention to treat analysis will be undertaken replacing missing 3 and 12 month water temperatures (excluded participants and those where access could not be gained to homes for temperature measurement), with baseline temperatures, or where baseline temperatures are unavailable they will be replaced by the mean or median temperature for that treatment arm, dependent on the distribution of the temperatures.

The proportion of families with a bath hot water temperature ≤ 46 degrees Celsius will be compared between treatment arms using χ^2 ^tests and logistic regression to estimate the odds ratio and its 95% CI. Outcomes measured on an ordinal scale will be compared between treatment arms using χ^2 ^tests for trend, or will be dichotomised and analysed as binary variables depending on the distribution of responses.

Sensitivity analyses will be undertaken to examine the effect of adjusting for baseline temperature. Where baseline temperatures are unavailable they will be replaced by the mean or median temperature for that treatment arm, dependent on the distribution of the temperatures. These analyses will be undertaken using linear regression or a Mann-Whitney U test based on change scores.

The proportion of families in the intervention arm who have TMVs removed, replaced or repaired and who adjust the temperature setting of the TMV will be described using proportions and 95% CI.

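### At 3 months the baseline-adjusted sensitivity analysis cannot work as written: no sampled family has a baseline temperature, and filling in the arm mean makes the covariate a linear function of treatment arm

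*Protocol article*

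**What the plan says.** Four parts of the protocol article bear on this point.

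- **Baseline data collection:** "The first 50% of participants recruited to each arm will have their bath hot tap water temperature measured at recruitment to the trial".
- **Follow-up data collection, Primary outcome measure:** the 3-month sample is "A random sample of 15 families in each arm, who did not have their tap water temperature measured at baseline". For 12 months, "a separate random sample of 15 families in each arm will be selected to have their tap water temperature measured at 12 months", and the no-baseline condition is not repeated.
- **Sample size:** "A different 15 families in each arm will be tested at 3 and 12 months", and "a total of 120 participants will be recruited". The Randomisation section allocates equal numbers to the arms.
- **Analysis:** "Sensitivity analyses will be undertaken to examine the effect of adjusting for baseline temperature". Unavailable baselines take the mean or median of the family's treatment arm. The method is linear regression or a Mann-Whitney test on change scores. The intention-to-treat rule in the same section replaces a missing 3- or 12-month temperature with the family's baseline and, failing that, with the arm's mean or median.

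**The concern.** The sampling rule removes from the 3-month sample the variable that the sensitivity analysis adjusts for. The fill-in rule then puts back a value that carries only the treatment arm. A pre-specified robustness check on the primary outcome would give either no estimate, or a change-score result whose error rate is not the nominal one. Substituting the baseline for a missing follow-up value depends on the same absent reading. These are stated rules that conflict, not details left to a later analysis plan. Once the samples have been drawn and valves fitted, the missing baselines cannot be recovered.

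**Working it through.** **The plan's own figure.** Inputs from Sample size: means 60.4 and 46 °C (difference 14.4), SD 9.1, 90% power, two-sided 5%. A t-test has power 88.3% with 9 per arm and 91.7% with 10, so 10 per arm is reproduced. Allowing for 33% losses, 10/0.67 = 14.9, hence 15. The sample size is not in dispute.

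**Who has a baseline.**
- Per arm: 120/2 = 60 families; half, 30, are measured at baseline and 30 are not.
- 3 months: 0 of 15 per arm have a baseline, by rule.
- 12 months, if the restriction carries over: 15 + 15 = 30 uses up exactly the 30 unmeasured families, so again 0 of 15.
- 12 months, if it does not: the draw is from the 60 − 15 = 45 remaining families, 30 of them measured. The expected number with a baseline is 15 × 30/45 = 10 of 15; the chance of none is 1/C(45,15), about 3 × 10⁻¹².

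**Linear regression at 3 months.** Let T be 0 for control and 1 for intervention, and let m₀ and m₁ be the arm baseline means. The filled covariate is B = m₀ + (m₁ − m₀)T, a linear combination of the intercept and T. The matrix [1, T, B] has rank 2, so the coefficients of T and B cannot be separated. With even one observed baseline per arm the rank was 3 when checked. Filling with the overall mean does not rescue a sample that has no baselines: B is then a constant, and nothing is adjusted for.

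**Change scores at 3 months.** With every baseline filled, the between-arm difference in change is the raw difference minus (m₁ − m₀). No within-arm variation is removed. Assumptions: SD 9.1 at both times, 30 readings per arm, filling by the mean, normal data, no true effect.
- SD of the added shift: 9.1 × √(2/30) = 2.35 °C; 95% range ±1.96 × 2.35 = ±4.6 °C.
- t-test on change: ratio of true to nominal standard error = √[(2/15 + 2/30)/(2/15)] = √(0.200/0.133) = 1.22. Type I error = P(|t₂₈| > 2.048/1.22), about 10.6%.
- Mann-Whitney on change, 10,000 simulated trials: 9.5%, against 4.4% for the same test on unshifted temperatures.

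**Missing follow-up values.** At 3 months no sampled family has a baseline to substitute, so the first step of the intention-to-treat rule never applies and every missing value goes to the arm mean or median. The planned loss is 33%.

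**The case against.** Several points on the other side stand.

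- **12 months.** A reader might infer that no followed-up family at either time has a baseline. The count of 30 favours that reading, but the restriction is written only for the 3-month sample. The intention-to-treat rule also presupposes that some followed-up families have a baseline. If the 12-month sample is drawn from all remaining families, the regression there can be fitted.
- **Cannot be run at all.** This is too strong. The change-score test is computable; it is uninformative as an adjustment.
- **Importance.** This is a sensitivity analysis. The 2.35 °C shift is about one-sixth of the planned 14.4 °C difference (2.35/14.4 = 0.16), and the inflated error rates apply only if there is no true effect.
- **Baseline timing.** The allocation letter is to "provide details of how they will be contacted by GHA to organise water temperature measurement and TMV fitting". A reader might infer that baselines are taken after allocation is known. The text does not say which measurement is meant, and Baseline data collection places the reading at recruitment, so this is not established.
- **Wasted baseline visits.** These readings can still describe how comparable the arms are, and the reading at an outlet other than the bath serves to detect thermostat changes.
- **Deliberate non-overlap.** The Background reports a campaign in which only half of those who tested their water and found it above 54 °C lowered the thermostat. A baseline visit could prompt the same, so keeping measured families out of follow-up may be a safeguard, although the article gives no reason.

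None of this rescues the 3-month regression, which fails whatever the data show.

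**Conclusion.** Wrong as written, of moderate severity. At 3 months the adjusted regression is not estimable; this follows from the sampling and fill-in rules alone and needs no numerical assumption. The change-score alternative adjusts for nothing within arm and adds chance error that the test ignores. Its size (SD 2.35 °C; type I error about 9.5% for Mann-Whitney, 10.6% for a t-test) rests on the assumed SD and number of baseline readings. The same holds at 12 months only on the unstated reading that the restriction covers that sample too. The primary unpaired t-test on observed temperatures is not affected, and the documents support no claim that the trial's main comparison is compromised by this conflict.

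**What to change.** Reconcile Baseline data collection, Primary outcome measure and Analysis before the follow-up samples are drawn, and state whether the 12-month sample may include families with a baseline.

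1. **If the non-overlap is deliberate:** for every sample without baselines, delete the baseline-adjusted and change-score analyses and the substitution of baseline for missing follow-up temperatures. This costs a few sentences.
2. **If a follow-up sample includes families with a baseline:** say so, adjust by ANCOVA in that sample, and fill any remaining missing baselines with the overall mean across both arms, never the arm mean.
3. **Optional redesign:** draw the 15 + 15 families per arm from the 30 who have a baseline. This adds no visits, but its downside must be stated. The visit may prompt families to lower the thermostat. That would mainly cool control homes, because the valve already caps the bath tap in the intervention arm, and so would shrink the difference. It also replaces a later-recruited sample with an earlier-recruited one; neither biases the comparison as long as both arms are treated alike.

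The first two options change text only.

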### Outcome measures

#### Definition of primary and secondary outcome measures

The primary outcome measure will be the bath hot tap water temperature at 3 and 12 months post installation of TMV (intervention group) or post randomisation (control group).

Secondary outcome measures will include:

a) Intervention arm only:

• TMV problems (failures, replacements, repairs or removals and reasons why TMVs are repaired, replaced or removed).

• Adjustment of temperature setting of TMVs by families.

• Satisfaction with TMVs.

• Cost of fitting TMVs and of any TMV problems.

b) Both intervention and control arms:

• A bath hot tap water temperature = 46 degrees Celsius.

• Satisfaction with bath hot tap water.

• Bath time safety practices (e.g. bath time supervision, use of other methods to increase bath water temperature, checking bath water temperature).

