##### Secondary outcome measures

Secondary outcomes will be measured at 12 months post installation of TMVs (intervention arm) and at 12 months post randomisation (control arm). Data will be collected by questionnaire, which families can choose to complete by telephone or by post. The follow-up questionnaire will include questions on bath time safety practices, bath time supervision and satisfaction with hot water supply. Intervention arm families will also be asked questions about satisfaction with the TMV and the fitting process, attempts to adjust the TMV temperature setting, TMV problems, occupational details and work time lost as a result of TMV fitting or problems. TMV problems will also be ascertained from repair requests or complaints made to GHA by families. Families who complete the follow-up questionnaire will be offered a £5 gift voucher for use in local stores to increase response rates [22].

The design of the follow-up questionnaire will be informed by interviews with a sample of approximately 15 families in rented social housing who have had TMV valves fitted. A purposive sample of families will be obtained, as described above, but also, if possible, to include families with differing sites of installation of TMVs, and those who have experienced TMV failures. Interviews will be used to explore families' attitudes towards TMVs, experiences of using TMVs, attempts at altering temperature settings on TMVs and any changes in safety behaviour or bath time supervision following the fitting of TMVs. They will also be used to inform the development of questions on satisfaction with TMVs, bath time safety and supervision.

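### The outcome, sample-size and analysis sections list different valve events; the analysis omits failed and disabled valves, so it does not estimate the proportion the 6.5% limit applies to

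*Protocol article*

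**What the plan says.** All references are to the protocol article.

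- **Definition of primary and secondary outcome measures**, intervention arm only: "TMV problems (failures, replacements, repairs or removals and reasons why TMVs are repaired, replaced or removed"). A separate outcome is "Adjustment of temperature setting of TMVs by families".
- **Sample size**: the claim to be tested is that "the proportion of TMVs removed, disabled or whose temperature setting was adjusted did not exceed 6.5" per cent. The section gives n = 50 per arm, a one-sided 5% test, 80% power and an assumed true value of 1%.
- **Analysis**: the proportion of intervention families "who have TMVs removed, replaced or repaired and who adjust the temperature setting of the TMV will be described using proportions", with a 95% CI.
- **Secondary outcome measures** (follow-up): the 12-month questionnaire asks intervention families about TMV problems and about attempts to change the setting. In addition, "TMV problems will also be ascertained from repair requests or complaints made to GHA by families".
- **Primary outcome measure** (follow-up): a plumber measures the bath tap temperature in a random 15 families per arm at 3 months and in a separate random 15 per arm at 12 months. The Analysis section compares the proportion at or below 46 °C between arms.

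**The concern.** The three sections should describe the same events, or say why they differ. They do neither. A named outcome (failure) and one component of the sized hypothesis (disabling) are both missing from the sentence that says what will be reported.

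This matters for two reasons. First, the trial is partly sized on showing that few valves are removed, disabled or adjusted, yet no planned estimate corresponds to that claim. Second, the omitted events are those least likely to show up under another label. A failed valve that is replaced or repaired is still counted, but one left in place is not. The objectives include potentially adverse effects of fitting, among them families no longer checking the water because they assume it is safe. An understated problem rate would therefore bear on the safety message as well as on acceptability.

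**Working it through.** **1. The event lists side by side**

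| Event | Outcome definition | Sample size hypothesis | Analysis sentence |
|---|---|---|---|
| Failed | yes | no | **no** |
| Disabled | no | yes | **no** |
| Removed | yes | yes | yes |
| Replaced | yes | no | yes |
| Repaired | yes | no | yes |
| Setting adjusted | yes, as its own outcome | yes | yes |

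The analysis list matches neither of the others. Against the outcome definition it loses failures. Against the hypothesis it loses disabled valves and gains replaced and repaired ones. Whether the analysis sentence means one composite or several proportions, none of them is the proportion removed, disabled or adjusted.

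**2. The plan's own figure**

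Inputs from Sample size: n = 50, limit 6.5%, true proportion 1%, one-sided 5%, 80% power. I read the test as rejecting a proportion of 6.5% or more in favour of a lower one, by the exact binomial.

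- P(0 events | 6.5%) = 0.935^50 = 0.035.
- P(0 or 1 event | 6.5%) = 0.035 + 50 × 0.065 × 0.935^49 = 0.155.
- So at n = 50 the only rule with error at or below 5% is zero events.
- Power of that rule at 1% = 0.99^50 = 0.605.

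The stated 80% is not reproduced. The smallest n reaching it exactly is 72 (at most one event, error 0.048, power 0.838). A normal approximation with the null and alternative exchanged gives n = 46, with 82% power at 50. This is a separate matter, and the present point does not depend on it.

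**3. Sensitivity to uncounted valves**

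- Zero counted events in 50 gives a one-sided 95% exact upper bound of 1 − 0.05^(1/50) = 5.8%, below the limit. One event gives 9.1%, above it.
- With all 60 intervention families (half of 120), the rule is still zero events: 0 events p = 0.018, 1 event p = 0.092.
- The 95% CI that the Analysis section plans, if two-sided and exact, runs for 0/50 from 0 to 1 − 0.025^(1/50) = 7.1%. This includes 6.5% even with no events, so the planned interval does not stand in for the one-sided test.

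If a share m of events goes uncounted, the chance of seeing none is (1 − p(1 − m))^50. The values of m are assumptions.

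| True proportion p | m = 0 | m = 0.5 | m = 0.75 |
|---|---|---|---|
| 6.5% | 3.5% | 19% | 44% |
| 10% | 0.5% | 8% | 28% |

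**4. What the temperature readings can add**

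Readings cover 15 + 15 = 30 of about 60 intervention homes, each measured at one follow-up time. The chance that 15 homes include at least one faulty valve is 1 − (1 − p)^15: 54%, 79% and 96% for assumed rates of 5%, 10% and 20%. The readings are a useful partial check, but nothing in the article links them to the valve-problem outcome.

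**The case against.** The strongest reply is that this is one summary sentence in a condensed article, which refers to a pre-specified analysis plan that is not shown. That plan may list failures and disabled valves. This limits how much can be inferred about what will be done, but it does not remove the conflict among three sections of the article itself.

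Several stronger readings are tempting, and the article does not support them.

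- *Failed or disabled valves are treated as trouble-free.* No section says so. Failures are a named outcome and the questionnaire asks directly about problems, so a reported failure is collected. It is simply not in the list to be analysed.
- *A valve passing hot water goes unseen.* Temperature at or below 46 °C is already an outcome, and its complement shows hot readings in the measured homes. The limits are coverage and the missing link to this outcome.
- *About 20 of 50 valves would be non-functioning*, taking the 60% still in place and working in one study cited in the Background. The other 40% includes valves no longer fitted, and removals are counted here. That study fitted devices in only 37 homes and was uncontrolled.
- *Four missed valves are needed to matter*, because 6.5% of 50 is 3.25. That compares a point estimate with the limit. The stated one-sided test turns on one event.

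It can also be said that the lists serve different purposes, household rejection in one place and technical faults in another. This stands in part. It is a reason not to merge everything into one definition, since failures and repairs would then enter a hypothesis set at 1% against 6.5% without justification.

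**Conclusion.** The point holds as an inconsistency of definition with a consequence for the reported estimate. The analysis sentence omits one named outcome event and one component of the sized hypothesis. The proportion it yields can be too low for failed or disabled valves left in place, and it is not the quantity to which the 6.5% limit applies.

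On size, one uncounted disabled valve among 50 can turn a result that does not support the claim (p = 0.155) into one that does (p = 0.035). This assumes the exact one-sided test and about 50 evaluable valves. How many events would go uncounted is not given in the documents, so the probabilities under partial counting are illustrations only.

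The outcome is secondary, and the primary temperature comparison is unaffected.

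**What to change.** In the Analysis section, replace the valve sentence with three separate results for the intervention arm:

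1. The proportion of valves removed, disabled or adjusted, defined exactly as in Sample size, set against the 6.5% limit with a one-sided 5% exact test or the equivalent upper bound.
2. The proportion with any TMV problem as in the outcome definition (failed, replaced, repaired or removed), with a 95% CI.
3. Among homes with a fitted TMV and a follow-up reading, the proportion with bath tap water above 46 °C, with its CI, cross-tabulated against reported problems and reported adjustment.

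Result 3 should not be folded into 1 or 2. Only about half of the intervention homes are measured, so merging would give measured and unmeasured homes different chances of detection. A reading above 46 °C can also reflect an adjustment that is already counted.

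Add disabling to the listed outcomes, so that result 1 has a stated outcome behind it.

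The cost is a change of wording and one extra tabulation of readings already planned. The reported problem rate may look less favourable.
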